### Associations between ethnicity, occupation and COVID-19 outcomes

The relationship between ethnicity and COVID-19 outcomes will be assessed using Poisson, logistic and flexible parametric time-to-event regression models (table 3: COVID-19 outcomes and definitions, identified via listed data sources, to be asessed in UK HCW cohort and within listed subgroups, via listed analysis approach in the planned study). For each outcome, multivariable models will incorporate ethnic category and occupational group, and their interactions, adjusted for the four core predictors. The analyses will be conducted by country, and country-specific results combined using meta-analysis methods to produce UK estimates. We will report incidence rate ratios, ORs or HRs with 95% CIs and p-values. Forest plots and cumulative incidence curves will be produced. Interactions between ethnicity and other predictors will be presented graphically to aid interpretation. Model assumptions will be assessed.

We will use directed acyclic graphs to map hypothesised causal associations between ethnicity, occupational group, the core predictors and COVID-19 outcomes. Mediation analysis methods will then be applied to disentangle the direct, indirect and mediated interactive effects of ethnic category and COVID-19 outcomes. The direct effects estimated using the approach are likely to be related to unmeasured explanatory factors, including experiences of structural discrimination and racism, rather than any genetic predispositions for differing outcomes.

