Given the differences in coverage and data across databases, the analysis will be twofold. First, a broad analysis will address the main objective using the full UK-wide cohort for any HCW employed or registered on 1 February 2020. Second, a detailed HR substudy will incorporate additional information on ethnicity, occupational role and potential for SARS-CoV-2 exposure (including whether an individual actively worked during the study period), and changes to these throughout the study period.

COVID-19 diagnosis, hospitalisation and mortality data will be gathered from several routinely collected EHR databases. We aim to obtain primary and secondary care data sets as well as specific intensive care audit data (such as Intensive Care National Audit & Research Centre data for England and Wales and Scottish Intensive Care Society Audit Group data for Scotland) and mortality information (Office for National Statistics, ONS) for each country. We also plan to incorporate specialised COVID-19 related databases, including COVID-19 surveillance data (COVID-19 Hospitalisation in England Surveillance System, CHESS), COVID-19 Symptom Study app data,^22^ and Public Health England (PHE) Pillar 1 (within hospital) and Pillar 2 (community-based) testing data, where available. Additional data sets, such as PHE Pillars 3 and 4, will be sought and incorporated if obtained.

It may not be possible to access all outcome data sets for England, Wales, Scotland and Northern Ireland. Therefore, outcomes will be assessed separately in each country and results combined using meta-analysis methods to produce UK-wide estimates.

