### Observation period

Follow-up commences on the index date (1 February 2020) (or date of return/commencement of employment for the HR substudy) and continue until either their death date (COVID-19 related or due to other causes) or the study end date (31 January 2021). For the HR substudy, those leaving NHS employment during the study period will be included up until this date, at which point they will be censored.

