### Predictors

We will investigate and adjust for the following core predictors: age, sex, comorbidities and socioeconomic deprivation. A description of the definitions for these core predictors, and how they will be assessed, is provided in table 4.

**Table 4 T4:** Definitions for core predictors associated with risk of adverse COVID-19 outcomes

Predictor	Definition
Age	A continuous measure of age (in years) at the index date (1 February 2020), calculated using date of birth as recorded in HR or professional registration databases.
Sex	A categorical measure (female/male/other) as recorded in HR or professional registration databases.
Comorbidities	A categorical measure counting the number of comorbidities for each individual (0, 1 or 2 or more) obtained from primary care records and supplemented with secondary care records in analyses conducted in the hospitalised cohort. Comorbidity count will incorporate conditions from the NHS Digital shielded patient list algorithm and others found to be associated with adverse COVID-19 outcomes.
Socioeconomic deprivation	An ordinal measure using quintiles of the Index of Multiple Deprivation (IMD), the official measure of relative deprivation for small areas in each country, based on residential postcode as recorded in HR or professional registration databases. Where residential postcode is not provided workplace postcode will be used as a surrogate.

HR, human resource; NHS, National Health Service.

Elevated body mass index (BMI), obesity and smoking are also considered key predictors for adverse COVID-19 outcomes;^9 23 24^ however, are likely to be missing for large proportions of the identified cohort. Furthermore, missingness in EHR data is unlikely to be random, preventing standard imputation approaches. Thus, BMI and smoking will not be included as independent predictors in the primary study but instead in a sensitivity analysis exploring COVID-19 outcomes within HCWs where this information is available in primary or secondary care medical records, within 24 months prior to the study start date.

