### Outcome incidence

Adjusted annual and quarterly incidence rates, per 100 000 HCWs, for each outcome will be calculated for each country where available. Meta-analysis methods will combine the country-specific estimates to give an overall UK incidence rate estimate. Adjusted incidence rates by ethnicity and occupation will be calculated in the same way. All incidence rates will be adjusted for the four core predictors (age, sex, comorbidities and deprivation) using standardisation methods. The incidence rates of each outcome will be reported as the rate of cases in the final UK HCW cohort and within subgroups who have experienced preceding COVID-19 events (table 3: COVID-19 outcomes and definitions, identified via listed data sources, to be assessed in UK HCW cohort and within listed subgroups, via listed analysis approach in the planned study). The time between diagnosis and outcomes will be summarised and cumulative incidence curves will be plotted.

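### The broad models have no region term within country, and meta-analysis of country rates need not return the incidence rate in UK healthcare workers

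*Protocol article*

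**What the plan says.** The association section of the Protocol article fixes the broad models: "multivariable models will incorporate ethnic category and occupational group, and their interactions, adjusted for the four core predictors". The Predictors section names those four: "We will investigate and adjust for the following core predictors: age, sex, comorbidities and socioeconomic deprivation". Country is the stratum, and country results are then pooled: "The analyses will be conducted by country, and country-specific results combined using meta-analysis methods to produce UK estimates". Neither region within country nor calendar period is among the terms.

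Location does enter elsewhere. Deprivation is a small-area index taken from residential postcode, or workplace postcode where that is absent (Table 4). Place of work is in the occupation model of the HR substudy. Hierarchical models for organisations and for hospitals are among the additional analyses, which depend on the numbers captured.

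On time: "Follow-up commences on the index date (1 February 2020) (or date of return/commencement of employment for the HR substudy"). Descriptive rates are planned by quarter as well as by year: "Adjusted annual and quarterly incidence rates, per 100 000 HCWs, for each outcome will be calculated for each country where available".

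On the UK rate, the Outcome incidence section says: "Meta-analysis methods will combine the country-specific estimates to give an overall UK incidence rate estimate". Rates by ethnicity and occupation are formed the same way. The same section describes the target: "The incidence rates of each outcome will be reported as the rate of cases in the final UK HCW cohort". Country-wise analysis is motivated by data access: "It may not be possible to access all outcome data sets for England, Wales, Scotland and Northern Ireland". The pooling model, scale and weights are not stated.

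**The concern.** There are two separate problems.

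**Region.** England is one stratum. If infection pressure differed between its regions and the ethnic mix of the workforce differs too, part of an ethnicity association reflects place. A deprivation quintile ranks areas by relative deprivation and does not measure local infection pressure. Place of work is not listed for the substudy's ethnicity model, and the clustering analyses are conditional extras. The regulator registries hold less workplace information, so an organisation model may not cover the broad cohort. Unadjusted geography would also enter the direct effects of the mediation analysis, which the plan expects to relate to unmeasured factors such as structural discrimination.

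**UK rate.** The rate of cases in a defined cohort is total cases over total people. A meta-analytic mean is a different quantity whenever country rates differ. At these sample sizes sampling error is small beside any real difference between countries, so random-effects weights become almost equal per country whatever the headcount.

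**Working it through.** **The plan's own figures (Sample size section).** 1.4 million × 6.2% = 86 800 infected (stated 86 600). 86 600 × (1 − 0.63) = 32 042 diagnosed, as stated. Diagnosed rate: 32 042 / 1 400 000 = 2289 per 100 000. These figures are not in dispute; they are used as inputs.

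**1. Region.** The documents give no regional data, so the following are assumptions: one high-rate region holds 20% of staff, with minority share *h* there and *l* elsewhere, and its rate is *r* times the rate elsewhere. Ethnicity has no true effect.

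- Overall minority share M = 0.2*h* + 0.8*l*
- Share of minority staff in the region: m = 0.2*h* / M
- Share of White staff in the region: w = 0.2(1 − *h*) / (1 − M)
- Spurious IRR = (1 + m(*r* − 1)) / (1 + w(*r* − 1))

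The plan's 79.2% White implies 20.8% non-White, so mixes should give M of about 20-21%.

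| h / l | M | m | w | IRR, r = 1.25 | IRR, r = 2 |
|---|---|---|---|---|---|
| 40% / 15% | 20% | 0.400 | 0.150 | 1.100/1.0375 = 1.06 | 1.400/1.150 = 1.22 |
| 45% / 15% | 21% | 0.429 | 0.139 | 1.107/1.035 = 1.07 | 1.429/1.139 = 1.25 |

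If both groups have the same regional distribution, the spurious IRR is 1.00.

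For comparison, take the expected random error of the diagnosis IRR, with 32 042 cases split as the workforce (White 79.2%, Asian 10.0%, Black 6.1%). The 95% factor is exp(1.96 × √(1/3204 + 1/25 377)) = 1.04 for Asian and exp(1.96 × √(1/1955 + 1/25 377)) = 1.05 for Black. Bias of the size tabulated would exceed the half-width of the interval.

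**2. UK rate.** Two units: England and Wales, 1.4 million at 2289 per 100 000 (from the plan), and Scotland, 163 000 (Table 1) at an assumed multiple of that rate. The population rate is total cases over total healthcare workers. Pooling is inverse-variance fixed effect and DerSimonian-Laird random effects, each on the log and raw scales.

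| Scotland's multiple (assumed) | Population rate per 100 000 | Random effects vs population | Fixed effect vs population |
|---|---|---|---|
| 1.0 | 2289 | 0% | 0% |
| 0.9 | 2265 | −4% | about 0% |
| 0.8 | 2241 | −8% to −9% | −0.5% to +0.2% |
| 0.7 | 2217 | −12% to −14% | −1.2% to +0.5% |
| 0.5 | 2169 | −21% to −25% | −4.5% to +1.6% |

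Where the rates differ, random-effects weights are about 50:50, against a headcount of 90:10. At a multiple of 0.5 the random-effects results are 1717 (95% CI 595 to 2838, raw) and 1619 (821 to 3193, log); both intervals contain 2169.

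With four units and an assumed split (1.3 million, 100 000, 163 000 and 60 000) and assumed rates, random effects is 11% to 15% low, with about 25% weight per country. Fixed effect is between −3.4% and +1.4%.

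**3. Calendar time.** The broad cohort shares one start date and one end date, so ethnic groups cover the same calendar period. That does not hold inside the Table 3 subgroups defined by an earlier COVID-19 event. Illustration with assumed inputs: case fatality 10% early and 3% later, with 30% of White cases early against 40% to 50% of minority cases. This gives a spurious odds ratio of 1.15 to 1.29. With equal early shares it is 1.00.

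**The case against.** Several objections stand.

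- A reader might infer that country is the plan's only geographic term. It is not: deprivation is a small-area measure, and place of work and the organisation and hospital models appear elsewhere. The gap is specific to the broad main models.
- A reader might infer that every main model lacks a needed calendar term. In the closed broad cohort, time since index is calendar time, and a whole-cohort logistic model over a fixed window has no quarter of follow-up to stratify on.
- A reader might infer a UK rate that is far off yet looks precise. In these examples no pooling option is both: random effects can be far off but its intervals contain the population rate, and fixed effect is tight but within about 5%.
- A larger spurious IRR, up to 1.35, needs a 45%/10% mix. That implies 17% minority staff overall, below the plan's 20.8%.
- The regional inputs are all assumed, and the formula gives no credit for confounding removed by deprivation or occupation.
- The pooling model is unstated and may be settled in a fuller analysis plan.

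The strongest objection is that place may lie on the pathway from ethnicity to outcome, so adjusting for it changes the estimand. That argues against replacing the unadjusted estimate. It does not argue against showing both, which lets the reader see how much of the association is geographic.

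**Conclusion.** The point holds in two limited parts.

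First, the broad main models leave within-country geography unadjusted. The bias could be about 1.06 to 1.25 on the IRR scale under assumed mixes consistent with the plan's workforce, against a random-error factor of 1.04 to 1.05. Whether bias of that size exists cannot be shown from the documents.

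Second, the Outcome incidence section names the rate in the UK cohort but obtains it by a method that need not return it. The shortfall is about 4% to 25% under random effects for the assumed Scottish rates, within about 5% under fixed effect, and nil if country rates are equal.

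Calendar time matters only in the subgroups defined by a prior COVID-19 event and in the HR substudy, where entry and exit are staggered. The documents do not support a claim that it biases the whole-cohort analyses.

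**What to change.** 1. Derive region from the postcode already required for the main analysis, add it to the broad main models, and report estimates with and without it.
2. Add calendar period of diagnosis or admission in the Table 3 subgroups defined by a prior COVID-19 event, and calendar time in the HR substudy. Leave the whole-cohort models without it.
3. Compute UK incidence, overall and by ethnicity and occupation, as the sum of country-specific standardised rates weighted by healthcare-worker numbers, over the countries with data for that outcome, and name those countries. Keep meta-analysis for effect ratios.

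The cost is plan wording, one derived variable and a few more parameters, which is negligible at this sample size. Region must be retained when postcodes are removed at anonymisation, so this has to be settled before the data are released to the analysts.

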### HR sub-study

We will conduct the analysis separately for all countries where both HR and outcomes data are available, country-specific results will be presented.

Each outcome will be evaluated using the same regression methods above. Multivariable models will incorporate ethnicity, occupation and the core predictors as before, while extended to incorporate additional predictor information. An ethnicity model will additionally adjust for religion, nationality and country of birth and incorporate their interactions with ethnicity, if appropriate. An occupation model will additionally adjust for primary area of work, role description, patient/non-patient facing, time in current role, place of work, pay grade and seniority. Finally, a COVID-19 exposure model will additionally adjust for absence information and total hours worked as time varying exposures, to assess the impact of changes in COVID-19 exposure over time. Forest plots and cumulative incidence curves will be produced. Interactions between ethnicity and other predictors, and the effects of time varying predictors, will be presented graphically to aid interpretation.

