### Outcomes

The main outcomes are COVID-19 diagnosis (confirmed and suspected, confirmed only), hospitalisation (all, COVID-19 specific, ITU admission) and mortality (all-cause, COVID-19 specific). The definitions, data sources and a summary of planned analyses for these outcomes are provided in table 3: COVID-19 outcomes and definitions, identified via listed data sources, to be assessed in UK HCW cohort and within listed subgroups, via listed analysis approach in the planned study.

**Table 3 T3:** COVID-19 outcomes and definitions, identified via listed data sources, to be assessed in UK healthcare worker cohort and within listed subgroups, via listed analysis approach in the planned study

Outcomes		Definitions	Data sources	Subgroups	Analysis approach (output)
COVID-19 diagnosis	Confirmed COVID-19 diagnosis	A positive swab test for SARS-CoV-2 during the study period	PHE Pillar 1 (PHE laboratories or NHS hospital) and Pillar 2 (wider population) testing data^1^		Poisson regression (IRR)
	Suspected COVID-19 diagnosis	Self-reporting of either a positive SARS-CoV-2 test or combination of symptoms shown to be predictive of positive testing^2^ during the study period or suspected case SNOMED CT codes (NHS Digital) recorded during the study period	COVID-19 Symptom Study app and primary care data		Poisson regression (IRR)
Hospitalisation	All hospitalisations	Any hospital admission recorded during the study period	Secondary care and CHESS data	Confirmed COVID-19 diagnosis	Logistic regression (OR)
	COVID-19 hospitalisations	hospital admissions with COVID-19-specific ICD-10 codes^3^ during the study period or positive swab test for SARS-CoV-2 recorded during or within 28 days prior to admission	Secondary care, CHESS, PHE Pillar 1 (PHE labs or NHS hospital) and Pillar 2 (wider population) testing data^1^	Confirmed COVID-19 diagnosis	Logistic regression (OR)
	COVID-19 ITU admissions	Admissions to ITU during the study period	Secondary care, CHESS, and intensive care audit data	Confirmed COVID-19 diagnosis	Logistic regression (OR)
Mortality	All-cause mortality	Any death registration recorded during the study period	ONS mortality, primary care and secondary care data	Confirmed COVID-19 diagnosis COVID-19 hospitalisations COVID-19 ITU admissions	Flexible parametric time-to-event regression (HR)

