### HR sub-study

This sub-study will consider only those undertaking active employment in the NHS during the study observation period and will be conducted only in regions where data are available.

Additional ethnicity-related predictors include religious belief, nationality, immigration status and country of birth. Additional occupation predictors include primary area of work, role description, full/part time, patient/non-patient facing,^18^ time in current role, organisation type, salary grade, length of service and seniority. Additional exposure-related predictors include absence information and total hours worked. Changes in these predictors will be captured throughout the study period. Time varying covariates will be incorporated to enable the assessment of the impact of changes in COVID-19 exposure over time.

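### HR sub-study: logistic regression is carried over for hospitalisation and ITU admission although entry, censoring and covariates vary over time; the absence exposure has no stated lag

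*Protocol article*

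**What the plan says.** **Model.** Table 3 (Outcomes) gives logistic regression with an odds ratio for all three hospitalisation rows: any admission, COVID-19 admission and ITU admission. Each is defined over one window common to everyone; the ITU row, for example, reads "Admissions to ITU during the study period". Diagnosis gets Poisson regression and mortality a flexible parametric time-to-event model. The HR sub-study section of the statistical analysis plan then says "Each outcome will be evaluated using the same regression methods above".

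**Follow-up.** Observation period starts everyone on 1 February 2020, "or date of return/commencement of employment for the HR substudy". It adds, for the sub-study, that "those leaving NHS employment during the study period will be included up until this date, at which point they will be censored".

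**Covariates.** The HR sub-study section under Methods says "Time varying covariates will be incorporated to enable the assessment of the impact of changes in COVID-19 exposure over time". The analysis section specifies that "a COVID-19 exposure model will additionally adjust for absence information and total hours worked as time varying exposures". Neither section gives a lag, a cut-off at diagnosis or a split by reason for absence. Study population removes only people on leave for the entire study period, so shorter sickness or isolation absence remains in the data.

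**The concern.** A logistic model with one record per person asks only whether the event occurred. It has no place for when someone came under observation, when they stopped, or what a covariate was on a given date. Someone employed for one month who then leaves counts as a non-event exactly like someone observed for the whole year. The sub-study's data structure and the model assigned to three of the seven Table 3 outcomes therefore do not fit together.

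Two things are at stake. First, if new starters, returners and leavers are spread unevenly across ethnic or occupational groups, the odds ratios mix risk with length of observation. Second, the exposure model, whose purpose is to show the effect of changing exposure, cannot be fitted for these outcomes.

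A secondary matter concerns the exposure model for any outcome. Infection commonly leads to absence. If absence enters at its current value, part of the outcome is being used to predict itself.

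**Working it through.** **1. The plan's own event counts** (Sample size).
- Infections: 1.4 million × 6.2% = 86,800 (stated 86,600, 0.2% apart).
- Diagnosed: 86,600 × (1 − 0.63) = 32,042 (as stated).
- Hospitalised: 32,042 × 25% = 8,010 (stated 8,000).

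The plan gives no figure for the sub-study models and none for staff turnover, so the inputs below marked as assumed are illustrative.

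**2. Effect of ignoring person-time.** Assume a constant hazard and that a share f of each group is observed for a uniformly distributed part of the year. Mean follow-up is then 1 − f/2. For a rare outcome the person-level odds ratio is close to

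true rate ratio × (1 − f₁/2) / (1 − f₀/2).

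With COVID-19 hospitalisation at the plan's 8,000 per 1.4 million:

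| Part-year share, reference vs comparison (assumed) | Mean follow-up (years) | OR if true ratio is 1.0 | OR if true ratio is 1.5 |
|---|---|---|---|
| 10% vs 10% | 0.95 vs 0.95 | 1.00 | 1.50 |
| 10% vs 20% | 0.95 vs 0.90 | 0.95 | 1.42 |
| 15% vs 30% | 0.925 vs 0.85 | 0.92 | 1.38 |
| 20% vs 40% | 0.90 vs 0.80 | 0.89 | 1.33 |

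For example, 0.90/0.95 = 0.947 and 0.80/0.90 = 0.889. At an assumed 8% a year for all admissions, the odds ratios under no true difference are 1.00, 0.94, 0.91 and 0.88. A model that uses person-time targets 1.0 and 1.5 in every row.

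**3. Comparison with sampling error.** Take 8,010 hospitalisations split by the plan's workforce shares (10.0% Asian, 79.2% White), with equal risk. The standard error of the log ratio is √(1/801 + 1/6,344) = 0.0375, so the 95% interval factor is exp(1.96 × 0.0375) = 1.08. A distortion of 5% to 11% is of similar size to the interval half-width, and a larger sample does not reduce it. Country-specific intervals would be somewhat wider.

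**4. Absence entered without a lag.** Simple arithmetic first: if 5% of person-time is absence and 30% to 60% of positive tests fall in absence (both assumed), the apparent rate ratio is (0.30/0.05)/(0.70/0.95) = 8.1 to (0.60/0.05)/(0.40/0.95) = 28.5, with no causal effect.

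A weekly simulation assumed 5% background absence, a truly protective effect of absence on infection (0.70), 25% of infections hospitalised a week later, and infection-related absence lasting three weeks:

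| Infections recorded as absence (assumed) | Diagnosis, same week | Diagnosis, 2-week lag | Hospitalisation, same week | Hospitalisation, 1-week lag | Hospitalisation, 3-week lag |
|---|---|---|---|---|---|
| 30% | 8.8 | 1.04 | 9.3 | 8.6 | 0.88 |
| 60% | 29.5 | 0.94 | 31 | 31 | 1.05 |
| 90% | 177 | 0.96 | 161 | 163 | 1.13 |

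The unlagged estimate points the wrong way. A one-week lag does not help for hospitalisation because it still falls after infection, so the lag has to be anchored before diagnosis, not before admission. The lagged values sit near 1 rather than 0.70 because background absence was drawn independently each week: the lag removes the reverse effect but does not by itself recover the protective one.

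Collapsing absence to a yearly total so that it fits a person-level logistic model does not solve this. In the same simulation the odds ratio per absent week was 1.29, 1.64 and 1.93.

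**5. Effect on the ethnicity estimate.** With unlagged absence in a Poisson model for diagnosis, the ethnicity rate ratio was 1.00 to 1.01 when the truth was 1.0, and 1.50 to 1.51 when the truth was 1.5. This included a scenario in which recorded absence after infection differed between groups (90% vs 60%).

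**The case against.** The strongest reply is that Table 3 says only logistic regression. It does not say one record per person, and pooled person-period logistic regression is a standard discrete-time model that handles delayed entry, censoring and changing covariates. That is correct, and it is one of the acceptable remedies. But the article mentions no person-period data and no offset, and it carries over unchanged the methods used where everyone has a common start. The sub-study models are described as extended, but only by adding predictors. The passages still have to be reconciled.

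It can also be said that a journal article condenses a fuller plan. For the choice of model this does not help, since the article fixes the method for every outcome and reaffirms it for the sub-study. For absence it carries more weight: lag and absence type may be set out elsewhere, and the article nowhere says that absence enters at its same-day value. What stands is that no lag or exclusion is stated and that current-value entry is the natural reading.

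Several stronger readings are tempting but not supported:
- *The broad-analysis odds ratios are equally affected.* There, follow-up has a common start and, deaths aside, a common end; staggered entry and censoring at leaving employment belong to the sub-study alone.
- *All sub-study outcomes are affected.* Poisson regression for diagnosis can take person-time, and the mortality model is time-to-event.
- *Absence distorts the ethnicity effect.* The check found almost no movement, and absence enters only the exposure model, not the ethnicity or occupation models.
- *Everyone hospitalised or dying is absent beforehand.* The document does not say so, and the outcomes include all-cause admissions and deaths.

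Employment length also matters less in the confirmed-diagnosis subgroup, where the relevant time runs from diagnosis.

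**Conclusion.** The inconsistency is real and confined to three outcomes in the HR sub-study. As an ordinary person-level model, the planned logistic regression cannot represent individual entry, censoring of leavers or time-varying covariates, so the exposure model cannot be fitted for hospitalisation and ITU admission. The bias in the odds ratios depends on turnover that the document does not report: about 5% to 11% in the unequal-turnover scenarios, essentially none if turnover is equal. Its direction depends on which group has less time in employment.

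The absence point is secondary. Under the assumed inputs, unlagged absence could turn a protective effect into a large apparent risk, which would defeat the exposure model's own purpose. The harm falls mainly on the absence estimate; the ethnicity estimate was hardly touched.

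**What to change.** In the HR sub-study section of the statistical analysis plan, state that hospitalisation (all and COVID-19) and ITU admission will be analysed by one of:
- Poisson regression with a log person-time offset and follow-up split where covariates change;
- the flexible parametric model already planned for mortality, with delayed entry and censoring;
- person-period logistic regression.

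Table 3 can keep its odds ratios for the broad analysis.

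For the exposure model, state that absence and hours worked are lagged to a window before diagnosis and, where reason codes exist, that COVID-19 sickness and isolation absence are separated from other absence.

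The cost is a few sentences. The first two options use model families already in the plan, and the entry, leaving and covariate-change dates are already needed for the sub-study. The downside is that sub-study results may become rate or hazard ratios and so will not match the broad-analysis odds ratios in kind; the report should say so. Lagging also discards a short stretch of early follow-up, and separating absence by reason depends on those codes being recorded.
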